## Abstract

**Background:**

Hepatocellular adenoma (HCA) in pregnant women requires special considerations because of the risk of hormone induced growth and spontaneous rupture, which may threaten the life of both mother and child. Due to scarcity of cases there is no evidence-based algorithm for the evaluation and management of HCA during pregnancy. Most experts advocate that women with HCA should not get pregnant or advise surgical resection before pregnancy. Whether it is justified to deny a young woman a pregnancy, as the biological behavior may be less threatening than presumed depends on the incidence of HCA growth and the subsequent clinical events during pregnancy.

We aim to investigate the management and outcome of HCA during pregnancy and labor based on a prospectively acquired online database in the Netherlands.

**Methods/design:**

The Pregnancy And Liver adenoma Management (PALM) - study is a multicentre prospective study in three cohorts of pregnant patients. In total 50 pregnant patients, ≥ 18 years of age with a radiologically and/or histologically proven diagnosis of HCA will be included in the study. Radiological diagnosis of HCA will be based on contrast enhanced MRI. Lesions at inclusion must not exceed 5 cm. The study group will be compared to a healthy control group of 63 pregnant patients and a group of 63 pregnant patients with diabetes mellitus without HCA. During their pregnancy HCA patients will be closely monitored by means of repetitive ultrasound (US) at 14, 20, 26, 32 and 38 weeks of gestation and 6 and 12 weeks postpartum. Both control groups will undergo US of the liver at 14 weeks of gestation to exclude HCA lesions in the liver. All groups will be asked to fill out quality of life related questionnaires.

**Discussion:**

The study will obtain information about the behaviour of HCA during pregnancy, the clinical consequences for mother and child and the impact of having a HCA during pregnancy on the health related quality of life of these young women. As a result of this study we will propose a decision-making model for the management of HCA during pregnancy.

**Trial registration:**

Dutch trial register: NTR3034

## Background

Hepatocellular adenoma (HCA) is rare benign tumor of the liver that occurs particularly in women during their reproductive years. The incidence is not exactly known. Studies performed years ago show an estimate incidence of 1-1.3 per 1,000,000 in women who have never used oral contraceptives (OC), compared to 30-40 per 1,000,000 in long-term users 
[1,2]. The association of HCA with the use of OC was first described in 1973 
[3]. In subsequent years many authors have supported the hypothesis of an association between OC and HCA 
[4-8]. The mechanism by which estrogen or other steroids contributes to the development of HCA is still not understood and studies are rare. Symptomatic patients with HCA present with right upper quadrant abdominal pain or discomfort secondary to bleeding within the HCA, elevated liver enzymes and symptoms of life treating hemorrhage into the peritoneal cavity. However, most patients with HCA are asymptomatic and present as an incidental finding during ultrasonographic examination of the abdomen for unrelated reasons or are noted during laparoscopic cholecystectomy. Despite its benign nature, the diagnosis of HCA has a great impact of the lives of these, mostly, young women because HCA can be complicated by hormone induces growth and rupture. Besides that malignant transformation of HCA into hepatocellular carcinoma has been reported with an overall frequency of 4.2% 
[9].

Regardless of the exact etiology and risk factors all female patients should be advised to stop OC’s and other hormone medication such as hormone replacement therapy, since regression of HCA may occur when steroids are withdrawn 
[10-13] and observation should be the first choice of treatment for most patients with HCA. Because of the risk for spontaneous rupture most authors believe that surgical resection is required if the diameter exceeds 5 cm after 6 months of follow-up without OC use, if the lesion does not show adequate regression after discontinuation of OC or if rebleeding occurs 
[14-17]. Surgical resection is also indicated if there is diagnostic doubt e.g. whether a tumor is malignant 
[18,19].

HCA in pregnant women requires special considerations because of the risk of hormone induced growth and spontaneous rupture, due to increased levels of steroid hormones during pregnancy that may threaten the life of both mother and child. Most experts advocate that women with HCA should not get pregnant or advise surgical resection before pregnancy 
[2,18]. Cobey et al. reported a maternal and fetal mortality risk of ruptured HCA during pregnancy of 44% and 38%, respectively 
[20]. However, all these cases were published in the 1970s and 1980s and nowadays the introduction and widespread use of highly advantage imaging modalities have probably decreased the doctors’ delay in the diagnosis of HCA. We recently proposed not to discourage all women with HCA from pregnancy, based on a study in which we monitored twelve women with documented HCA during a total of 17 pregnancies. In 4 cases HCA’s grew during pregnancy, requiring a Caesarean section in 1 patient (2 pregnancies) and radiofrequency ablation (RFA) in 1 case during the first trimester of pregnancy. All pregnancies had an uneventful course with a successful maternal and fetal outcome 
[21]. However, there is no evidence-based algorithm for the evaluation and management of HCA during pregnancy and labor, due to scarcity of cases. The conclusion not to discourage all women with HCA from pregnancy has, however, to be proven in a large multicentre study in which we will closely monitor pregnant patient with a HCA in a prospectively acquired database to give more insight in the behaviour of HCA during pregnancy.

## Methods/design

### Study objective

In this study we will investigate the management and outcome of HCA during pregnancy and labor based on a prospectively acquired online database in the Netherlands.

Main objective of the PALM-study

 • To investigate the incidence of HCA growth during pregnancy and labor.

Secondary objectives of the PALM-study

 • To investigate in which trimester of pregnancy growth of HCA occurs;

 • To investigate the degree of growth of HCA during pregnancy;

 • To investigate whether there is regression of HCA postpartum;

 • To investigate the HCA-related interventions during pregnancy and labor;

 • To investigate the incidence of bleeding of HCA during pregnancy and labor;

 • To investigate liver-related clinical signs during pregnancy;

 • To investigate elevated liver enzymes during pregnancy;

 • To evaluate the health related quality of life of pregnant patients with HCA;

 • To investigate whether there is a difference between health related quality of life of pregnant patients with HCA and pregnant patients with other comorbidity that have an indication for pregnancy care at the obstetrician in secondary care and healthy pregnant patients.

### Study design

The PALM-study is a multi-centre prospective study in three cohorts of pregnant women. The study started on November 1 2011 and inclusion of patients will be a period of minimal 3 to maximal 5 years. In total 50 pregnant patients with HCA < 5 cm will be included in the study. These patients will be compared to a healthy control group consisting of 63 pregnant patients without HCA and a group consisting of 63 pregnant patients with diabetes mellitus (DM). Approval of the Medical Ethics Committee of Erasmus Medical Centre was obtained, NL36058.078.11.

### Patient selection

#### Study group

Properly Dutch speaking, pregnant patients, 18 years of age or older with a radiologically and/or histologically proven diagnosis of HCA can be included in the study. Radiological diagnosis of HCA will be based on contrast enhanced magnetic resonance imaging (MRI) and if available in combination with (contrast enhanced) ultrasonography (US). Lesions must not exceed 5 cm. In the first weeks of pregnancy patients will be referred to the obstetrician for pregnancy care. Baseline starts at 14 (+/−3) weeks of gestation. At this day and every 6 weeks patients will undergo US of the HCA lesion at the radiologist. Before US of the HCA lesions patients will be asked to fill out generic health related quality of life questionnaires (12-item Short Form SF 12 and EuroQol questionnaire EQ-5d), a generic anxiety questionnaire (State-Trait Anxiety Inventory STAI-6) and the Impact of Event Scale (IES) questionnaire for thoughts and feelings about HCA around the US. One week afterwards the study group will be asked to fill out the STAI-6 en IES again. At 14 and 32 weeks of pregnancy patients will undergo venapunction.

#### Control group 1 (healthy pregnant patients without HCA)

Properly Dutch speaking, healthy pregnant patients, 18 years of age or older without HCA.

In the Netherlands, pregnant women will start pregnancy care with an independently practicing midwife early in pregnancy at the primary care level 
[22]. The midwife is responsible for the pregnant women as long as the pregnancy, labor or postpartum period is normal 
[23]. In case of complication, the midwife will refer the women to the obstetrician in secondary care 
[22,23]. Women with a high risk profile based on their medical or obstetric history will be cared for the obstetrician from the start of pregnancy 
[22,23].

Patients presenting at the practicing midwife will be asked to participate in the study. Thereafter, the patients will be included in the study by the study investigator. Patients will undergo US of the liver at 14 (+/-3) weeks of gestation to exclude HCA lesions in the liver. At this day and every other 6 weeks patients will be asked to fill out the SF-12 and EQ-5d questionnaire. At 14 and 32 weeks of pregnancy patients will undergo venapunction. In case of an uncomplicated pregnancy, the patient remains under the care of her practicing midwife during her pregnancy and postpartum.

#### Control group 2 (pregnant patients with Diabetes Mellitus)

Properly Dutch speaking, pregnant patients, 18 years of age or older with Diabetes Mellitus, can be included in the study. These patients have an indication for pregnancy care at the obstetrician in secondary care. Patients will undergo US of the liver at 14 (+/-3) weeks of gestation to exclude HCA lesions in the liver. At this day and every other 6 weeks patients will be asked to fill out the SF-12 and EQ-5d questionnaire. At 14 and 32 weeks of pregnancy patients will undergo venapunction.

For all groups informed consent is mandatory. A patient can always withdraw her consent at anytime during the study where after she is referred for the present standard of care.

### Hypothesis

Pregnancy may be allowed in case of one or more known HCA < 5 cm (without previous intervention), because a HCA < 5 cm will not disturb the course of pregnancy.

Disrupted course of pregnancy:

 • interventions during pregnancy (radiological and/or surgical intervention).

 • Decreased quality of life and/or anxiety in patients during pregnancy related to the presence of HCA in the liver and possible growth during pregnancy.

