### Power calculation

In our previous study we measured growth of HCA in 4 out of 17 pregnancies (24%) or in 3 out of 12 women (25%). On a yearly basis approximately 50 new patients with HCA are seen at the outpatient clinic of the Erasmus University Medical Centre. The expectation is that 5% (5) of these women get pregnant. The expectation is that a total of 50 pregnant HCA patients from different tertiary referral centres in the Netherlands can be included in the study during a period of 3 to maximum 5 years.

A difference of 0.5 Cohen’s D in health-related quality of life is a relevant difference 
[25]. We calculated that for this purpose 63 patients in both control groups have to be enrolled. A two-sample *t* test was performed with a two-sided significant level of 0.05 and a power of 0.80.

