Our main point of interest is whether it is justified to deny a young woman with a HCA < 5 cm a pregnancy. With this study we hope to obtain information about the behaviour of HCA during pregnancy and the impact of HCA during pregnancy on the life of these young women. Furthermore we hope to propose a decision-making model for the management of HCA during pregnancy.

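### The no-harm hypothesis cannot be supported by the one comparison the protocol states, a two-sided t test for a difference in quality of life

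*Protocol article*

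**What the plan says.** The Hypothesis section of the protocol article holds that pregnancy may be allowed with known HCA below 5 cm "because a HCA < 5 cm will not disturb the course of pregnancy". The Discussion repeats this. The Hypothesis section gives two forms of disrupted course. One is a radiological or surgical intervention during pregnancy. The other is "Decreased quality of life and/or anxiety in patients during pregnancy related to the presence of HCA in the liver" and its possible growth.

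The Power calculation section says that 0.5 Cohen's d "in health-related quality of life is a relevant difference", that "63 patients in both control groups have to be enrolled", and that a two-sample t "test was performed with a two-sided significant level of 0.05 and a power of 0.80". The 50 HCA patients come from expected recruitment. Under Study objective, the main objective is the incidence of growth, and a secondary objective asks whether quality of life differs between HCA patients and the two control groups. SF-12 and EQ-5d are collected in all three groups, STAI-6 and IES in the HCA group only (Table 1 footnote).

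The Discussion closes with the decision that the study is meant to inform: "Our main point of interest is whether it is justified to deny a young woman with a HCA < 5 cm a pregnancy".

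**The concern.** The hypothesis asserts an absence: no interventions and no loss of quality of life. The stated test takes absence as its null hypothesis. Rejecting the null would count against the hypothesis; failing to reject it leaves the matter open. A reader who pairs the hypothesis with the only test in the article could take p > 0.05 as confirmation, although that result becomes more likely as the sample shrinks. The same holds for events, where a low count in 50 pregnancies can look like safety while still allowing a rate that matters.

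The results are meant to feed a decision-making model and advice to women about becoming pregnant, so it matters whether the conclusion rests on what was excluded or only on what was not detected.

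**Working it through.** **Inputs.** From Power calculation: d = 0.5, two-sided alpha 0.05, power 0.80, 63 per control group, 50 HCA patients. From Retrospective cohort study: 17 earlier pregnancies, with RFA in 1 and Caesarean section in 2. No dropout is stated and none is applied.

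**1. The plan's own figure.** Normal approximation with equal groups: n = 2(1.960 + 0.842)² / 0.5² = 62.8, so 63 per group. The stated figure reproduces (63.8, so 64, by the noncentral t). It assumes 63 in the HCA group too.

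**2. Precision with 50 v 63.** In SD units:
- SE = √(1/50 + 1/63) = 0.189
- 95% half-width = t(0.975; 111 df) × SE = 1.982 × 0.189 = 0.375

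An observed deficit of 0.35 SD would be non-significant, yet its interval would reach 0.35 + 0.375 = 0.725 SD, well beyond the difference that the plan calls relevant.

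**3. How often a real deficit is missed with 50 v 63 (noncentral t).**

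| True deficit | P(non-significant) |
|---|---|
| 0.5 SD | 0.26 |
| 0.3 SD | 0.65 |
| 0.2 SD | 0.82 |

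Power at 0.5 SD is 0.744 (0.752 by the normal approximation).

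**4. A rule that can support the hypothesis.** Require the 95% interval for HCA minus control to lie wholly above -0.5 SD. The observed deficit must then be smaller than 0.5 - 0.375 = 0.125 SD. Observed deficits between 0.125 and 0.375 SD are inconclusive: not significant, but not excluding 0.5 SD either. If there is no true difference, power per comparison is Φ(0.5/0.189 - 1.960) = 0.75 (0.74 by the t distribution). For a margin of 0.3 SD it is Φ(0.3/0.189 - 1.960) = 0.35.

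**5. Interventions in 50 pregnancies.** For zero events the exact two-sided 95% upper limit is 1 - 0.025^(1/50) = 7.1%. The Clopper-Pearson limits for the next counts are 10.6% for 1 event, 13.7% for 2 and 16.5% for 3. With a true rate of 5%, zero events occur with probability 0.95^50 = 0.077; with 3%, 0.97^50 = 0.218.

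**6. Is zero a likely count?** At the earlier series' RFA rate of 1/17, P(0 in 50) = (16/17)^50 = 0.048. If the two Caesarean pregnancies count (3/17), (14/17)^50 is below 0.0001. Zero is therefore the most favourable case, not the expected one.

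**The case against.** The strongest reply has four parts.

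- **The t test is not offered as the test of the hypothesis.** It appears only where the control groups are sized, and the secondary objective on quality of life is worded as a search for a difference, which it fits. This stands: the t test is not the wrong test for that objective. The mismatch is with the hypothesis.
- **The article states no rule that treats non-significance or few events as proof of safety.** This stands. A reader might infer that the plan would conclude this way, or that it rewards low power, but no text says so. What can be said is that the stated elements leave the misreading open.
- **The study is mainly descriptive, in a rare disease, and an article may leave analysis rules and event ceilings to the full protocol or analysis plan.** This largely stands. The lack of a tolerable event rate is not an error in itself. But the hypothesis and the basis for the quality-of-life comparison are both printed here, and the second cannot support the first.
- **Part of the 26% is ordinary design risk.** Correct: at 63 v 63 the t test would miss a 0.5 SD deficit about 20% of the time (power 0.795). The rest comes from having 50 HCA patients.

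Bleeding also does not belong in the argument about the hypothesis: it is a separate secondary outcome, outside the definition of a disrupted course.

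**Conclusion.** The point holds in a limited form. The no-harm hypothesis includes no decrease in quality of life, and the only stated comparison can refute that but not support it. With the planned numbers a non-significant result is compatible with deficits larger than the plan's own relevant difference, and a true 0.5 SD deficit is missed about one time in four. Zero interventions would exclude only rates above 7.1%.

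These figures assume 50 and 63 analysed patients, equal SDs and no dropout; losses would widen every interval. They describe a single comparison, and requiring the rule to be met against both control groups lowers the joint power.

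The size of 0.5 SD is the document's own, but it is called a relevant difference and not a margin. Excluding it supports only the statement that there is no decrease that large, not that there is no decrease.

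**What to change.** - **Quality of life.** For SF-12 and EQ-5d, report the 95% confidence interval for HCA minus each control group. Claim no decrease as large as the stated relevant difference only if the interval lies wholly above -0.5 SD. Any stricter margin must be justified in advance and has lower power (about 0.35 at 0.3 SD).
- **The t test.** Keep it for the difference objective, and state that a non-significant result does not support the hypothesis.
- **Events.** Report interventions during pregnancy with exact 95% limits, and bleeding likewise as a separate secondary outcome. Reword the hypothesis from an absolute absence of disturbance to the rate that the data can exclude. If the clinical investigators want a ceiling, they should set it before seeing any outcome data; before data lock is too late, because centres enter outcomes throughout.
- **Anxiety.** STAI-6 and IES have no control data, so describe them within the HCA group and make no controlled claim.

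The cost is a reworded hypothesis and one decision rule, with no extra patients or visits. The downside is that the conclusion may be less favourable than a report of no significant difference, and an inconclusive result becomes possible.

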### Retrospective cohort study

We have previously reported that more than half of the HCA are discovered after the patient has sustained at least one pregnancy and none of these patients have reported problems during their pregnancies 
[19]. As mentioned above, recently we described a small but unique series of 12 women with documented HCA who were closely monitored during a total of 17 pregnancies between 2000 and 2009. In 4 cases HCA’s grew during pregnancy, requiring a Caesarean section in 1 patient (2 pregnancies) and RFA in 1 case during the first trimester of pregnancy to treat a hormone sensitive HCA, thereby excluding potential growth later on in pregnancy. No intervention was performed in the other 14 cases. All pregnancies had an uneventful course with a successful maternal and fetal outcome and we concluded that a “wait and see” management may be advocated in pregnant women presenting with HCA. In women with large tumours or in whom HCA had complicated previous pregnancies, surgical resection may be recommend 
[21]. However, additional data from different centres for the risk of hormone induces growth and rupture of HCA during pregnancy is needed.

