### Outcome measures

Primary outcome: Biological behaviour and clinical consequences of HCA < 5 cm during pregnancy. Growth is measured by repetitive US (and MRI in case of growth) at 14 (+/−3) and 20 and 26 and 32 and 38 weeks of gestation.

Secondary outcome: General health and pain scales as a measure for quality of life and anxiety related questionnaires for thoughts and feelings of adenomas around US. Other secondary outcomes are complications due to growth of the HCA during pregnancy possibly followed by interventions during pregnancy, incidence of hemorrhage and rupture of the HCA, incidence of liver-related clinical signs during pregnancy (itch, icterus), incidence of elevated liver enzymes during pregnancy.

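### The definition of a disrupted course of pregnancy leaves out HCA bleeding, rupture and HCA-related death, and is unclear on Caesarean section and on labour

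*Protocol article*

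**What the plan says.** All references are to the protocol article.

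- **Hypothesis.** Pregnancy may be allowed with one or more HCA < 5 cm "because a HCA < 5 cm will not disturb the course of pregnancy". A disrupted course is then defined by two items: "interventions during pregnancy (radiological and/or surgical intervention", and "Decreased quality of life and/or anxiety in patients during pregnancy related to the presence of HCA in the liver and possible growth during pregnancy". Nothing marks the list as a set of examples.
- **Background.** Pregnant women with HCA need special consideration "because of the risk of hormone induced growth and spontaneous rupture, due to increased levels of steroid hormones during pregnancy that may threaten the life"; this refers to mother and child alike. It cites "a maternal and fetal mortality risk of ruptured HCA during pregnancy of 44% and 38%, respectively", and adds that those cases were published in the 1970s and 1980s.
- **Study objective.** The secondary objectives include the incidence of HCA bleeding and the HCA-related interventions. Both are to be studied over pregnancy and labour.
- **Outcome measures.** The text reads "Primary outcome: Biological behaviour and clinical consequences of HCA < 5 cm during pregnancy", followed by how growth is measured. The secondary outcomes include "incidence of hemorrhage and rupture of the HCA".
- **Online database.** The fields include complications and their management, mode of delivery, and maternal and fetal outcome.
- **Retrospective cohort study.** Of 17 monitored pregnancies in 12 women, growth was seen in 4. It led to Caesarean section in two pregnancies of one woman and to radiofrequency ablation (RFA) in one case. "No intervention was performed in the other 14 cases".

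**The concern.** The definition gives content to the statement that a small HCA does not disturb pregnancy. Its two items are a procedure and a questionnaire result. The events that make clinicians discourage pregnancy now (bleeding, rupture, and death of mother or child) count only if they happen to lead to one of those two.

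An author who applies the printed definition could therefore class as undisturbed a pregnancy in which the HCA bled and was managed conservatively, or in which the child was lost because of the HCA before anyone could intervene. The study is meant to answer whether women should be told not to become pregnant and to yield a decision-making model. A definition that can misplace the key events weakens the summary figure most likely to be carried into that advice. If the treatment of Caesarean sections and of labour is left open, it can also be settled after the events are known.

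**Working it through.** **Step 1. Run each event through the printed definition.**

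| Event | Item 1: procedure in pregnancy | Item 2: quality of life or anxiety | Collected elsewhere? |
|---|---|---|---|
| HCA bleed or rupture treated by embolisation or resection in pregnancy | Counts | Possibly | Yes |
| HCA bleed or rupture managed without a procedure | Does not count | Only if the questionnaires show it | Yes (Study objective, Outcome measures) |
| HCA bleed or intervention in labour | Not on a literal reading of the window | Only if the questionnaires show it | Yes (Study objective) |
| HCA-related maternal death before any procedure | Does not count | No questionnaire can follow the event | Yes (Online database) |
| HCA-related fetal loss before any procedure | Does not count | Only if the questionnaires show it | Yes (Online database) |
| Caesarean section indicated by the HCA | Not stated | Only if the questionnaires show it | Mode of delivery yes; indication not listed as a field |

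The gap is thus confined to the second to fifth rows, with the sixth unclear. It is not hypothetical in the protocol's own terms: Outcome measures treats intervention as a possible, not a certain, sequel of a complication of growth.

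**Step 2. Compare the windows.** The Hypothesis counts interventions in pregnancy. The Study objective counts them in pregnancy and labour. An intervention at delivery is inside one window and, read literally, outside the other.

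**Step 3. Check how the earlier series treats Caesarean section.** The protocol's own growth figure reproduces: 4/17 = 23.5%, given as 24%. Pregnancies with an intervention: 17 - 14 = 3 = 2 Caesareans + 1 RFA. The protocol therefore counts Caesarean section as an intervention there. The same section calls the course of all 17 pregnancies uneventful, yet RFA in the first trimester is a disruption under item 1. The labels are not used consistently.

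**Step 4. Size of the Caesarean ambiguity, as illustration.** Exact (Clopper-Pearson) 95% limits for x events in n are:

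- lower = 0.025 quantile of Beta(x, n - x + 1)
- upper = 0.975 quantile of Beta(x + 1, n - x)

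| Reading | x/n | Rate | 95% CI |
|---|---|---|---|
| Caesareans counted | 3/17 | 17.6% | 3.8% to 43.4% |
| Caesareans not counted | 1/17 | 5.9% | 0.1% to 28.7% |

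Both Caesareans were in one woman, so pregnancies are not independent and these intervals are only a rough guide. Counted by women, the contrast is at most 2/12 (16.7%) against 1/12 (8.3%).

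**Step 5. Size of the main omission.** It cannot be computed. The document gives no incidence of bleeding, rupture or loss for HCA < 5 cm in pregnancy.

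**The case against.** The best reply is that nothing depends on these two items alone. The document does not make them a formal endpoint, test or decision rule. Bleeding is a named objective, haemorrhage and rupture are named outcomes, and maternal and fetal outcome are database fields. The abstract says the study will obtain information on the clinical consequences for mother and child. This stands: a reader might infer that the study fails to measure its most feared events or would hide a rupture, and the documents support neither.

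The literal gap is also narrow. The Discussion cites angioembolisation and resection for HCA haemorrhage in pregnancy, and both fall under item 1. This stands too, and limits the point to the rows in the working where no procedure takes place or the event falls in labour.

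On Caesarean section, one can say that it is plainly surgery and that the earlier series already counts it. That favours the 3/17 reading, but the Hypothesis does not say so and its window omits labour.

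Three further readings go too far:

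- The threefold contrast should not be projected onto the 50 planned patients. It rests on one woman, the intervals overlap heavily, and the document does not say that the series was limited to HCA < 5 cm.
- The 44% and 38% are mortality given rupture, in older cases. They show why rupture belongs in the definition, not how often it occurs.
- The primary outcome is loosely worded, but the sentence after it places growth there, so it does not simply miss the main objective.

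Finally, this is a condensed article and the full protocol may say more. That would excuse missing detail. It does not excuse a two-item definition that is printed in full and conflicts with other sections.

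**Conclusion.** The point holds as a defect of definition, not of data collection. The printed criterion for a disrupted pregnancy leaves out HCA bleeding or rupture managed without a procedure, events in labour, and HCA-related maternal or fetal death before any procedure. It does not say whether an HCA-indicated Caesarean section counts, and its window differs from that of the Study objective. Such pregnancies could be classed as undisturbed; the document does not show that they would be.

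The only part that can be sized is the Caesarean reading: 3/17 (17.6%) against 1/17 (5.9%) in the earlier series, as illustration. The effect of the main omission is unknown.

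The conclusion assumes that the two items are meant as the complete definition, as printed. It should be corrected before the hypothesis is assessed, but it does not threaten the validity of the data.

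**What to change.** In the Hypothesis section:

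1. Add to the definition HCA haemorrhage or rupture, however managed.
2. Add HCA-related maternal death and HCA-related fetal loss. The link to the HCA is needed; otherwise background fetal loss would count as disruption by the adenoma.
3. State that a Caesarean section or early delivery indicated by the HCA counts, in line with the count in the Retrospective cohort study section.
4. Use the window of the Study objective, pregnancy and labour, throughout.
5. Report quality of life and anxiety as a separate component, so that a questionnaire change and a rupture are not merged into one rate.

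This changes how events are classified, not how patients are managed. The cost is wording, and possibly one database field recording whether the HCA was the indication for delivery, since the listed fields give the mode of delivery but not its reason. The disruption rate may look less favourable as a result.
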